### Outcomes Assessment

Table 1 shows a breakdown of outcomes, methods for data collection, and evaluation metrics aligned with each aim. The table outlines how implementation and effectiveness will be assessed through mixed methods, ensuring that outcomes are aligned with the study’s overall evaluation framework. All surveys and interviews have been developed with feedback from the study’s in-country partners and will be administered with printed forms in either English or local languages as appropriate. The interviews will be administered by a researcher who is fluent in both English and the local language and trained to obtain consent before interviews.

Figure 2 illustrates all the methods of data collection used across the aims of this study, correlating with Table 1. An overview of each aim and a description of the methods used for data collection within them is detailed in the following sections.

**Figure 2 figure2:**
[figure not shown]
Overview of the mixed methods research tools used by aim. CFIR: Consolidated Framework for Implementation Research; IDI: in depth interview; KII: key informant interviews; NMED: National Malaria Elimination Division; PCR: polymerase chain reaction; QC: quality control; VCO: Vector Control Officers; VHT: village health teams.

### Aim 1: Evaluation of Contextual Determinants

We will assess the contextual determinants that influence implementation of the VectorCam platform by using an approach grounded in CFIR methodology and guided by established implementation mapping procedures [32]. This aim combines semistructured surveys and in-depth, pre- and post-key informant interviews (KIIs) to generate an understanding of the barriers and facilitators to successful implementation and evaluate the mechanisms through which they influence the implementation and effectiveness outcomes of interest.

Methods for data collection for Aim 1 include (1) CFIR-determinants evaluation survey with implementers, and (2) semistructured, pre- and post-KIIs to evaluate contextual characteristics with users. Firstly, for the CFIR-determinants evaluation surveys, we will administer a semistructured survey to select implementers: 4 MOH representatives and 6 VCOs or District Health Officials. This process will yield a total of 10 interviews conducted between months 4 and 6 of the staggered rollout. This survey will collect information on the context, probing for barriers and facilitators to implementation success. The survey instrument will primarily include Likert-scale questions to understand how the participant ranks the importance of specific determinants, supplemented by 5 open-ended questions to probe in-depth explanations for their choice of ranking. All questions are adapted from validated CFIR measurement tools to assess the 5 domains, including perceptions of intervention characteristics (eg, relative advantage and adaptability), inner setting (eg, organizational culture and implementation climate), outer setting (eg, external policies and community support), characteristics of individuals (eg, self-efficacy and knowledge), and process (eg, leadership engagement and planning).

Secondly, in each district, pre-KIIs will be conducted during the first week of intervention implementation (after training), and post-KIIs will then be administered 3 months later, focusing on the evaluation of contextual characteristics with users. Four VHTs and 2 VCOs will be purposely selected per district to ensure a balance of perspectives and varying levels of prior experience with entomological surveillance. The same participants will be contacted again for postimplementation interviews, enabling us to make paired comparisons of changes in attitudes and reported practices over time. Whenever possible, the same participants will be recontacted for follow-up interviews. If a participant is unavailable due to transfer, withdrawal, or other forms of attrition, a replacement participant occupying a similar implementation role will be purposively selected. Data collected through these sessions will inform iterative refinements to the implementation package and materials for subsequent adaptive cycles. By collecting rich qualitative data, the study team can examine what contextual determinants are most important during the initial phases of VectorCam rollout and, more precisely, how these factors are associated with changes in implementation outcomes.

### Aim 2: Acceptability, Feasibility, Fidelity, and Cost

The primary purpose of this aim is to ascertain the implementation outcomes of VectorCam use as defined by the Implementation-Outcome Framework [35]. Acceptability, fidelity, and feasibility of the implementation package will be assessed by using an integrated mixed methods approach that combines qualitative and quantitative data. For qualitative data, we will deploy pre- and postimplementation semistructured interviews, quarterly stakeholder engagement meeting notes, midpoint in-depth interviews with implementers and users, and FRAME-IS guided survey. Quantitative data collection tools for Aim 2 include data dashboard metrics, such as usage logs and percent completeness, and the field observation checklist. Additionally, the cost of VectorCam integration into Uganda’s vector surveillance system will be assessed with a combination of prospective costing methods, budget impact modeling, routine monitoring data, and structured feedback from district and national stakeholders. This aim will generate a comprehensive understanding of user experiences, protocol adherence, ease of use, fit with existing workflows, and evidence on the long-term financial feasibility of maintaining the implementation package at scale. Data from this aim can be used by Uganda’s MOH and its implementing partners to plan for a scalable and sustainable nationwide rollout.

Methods of data collection for Aim 2 include:

Semistructured pre- and post-KIIs to evaluate implementation outcomes with usersField observation checklist to evaluate fidelity and supervisory toolkitVectorCam app-system usage logsCosting database, budgets, and procurement recordsFRAME-IS documentation tool

The first data collection tool, pre- and post-KIIs, includes interview guides that are designed to be used at the same time points as the semistructured pre- and post-KII to evaluate context and administered to the same participants (ie, 4 VHTs and 2 VCOs) introduced in Aim 1 data collection methods. The purpose of this interview guide is to collect information about implementation outcomes. It will include structured questions for assessing satisfaction with the technology, perceived ease of use, alignment with existing workflows, confidence in the tool, and reflections on the frequency and consistency of use.

Each month, a VCO will use the second research tool and the field observation checklist to directly observe VHTs using the VectorCam system in the field to assess fidelity and the deployment of the supervisory toolkit. We will review these logs to verify the proportion of eligible VHTs trained in each cycle, equipment distribution, and posttraining support provided. The supervisory tool also contains a standardized field observation checklist and a set of structured questions designed to identify factors that may affect supervision, these questions will explore domains such as availability of logistical resources (eg, transport and devices), communication and coordination mechanisms, and context and barriers that will be used to assess how well VectorCam users are adhering to the protocol, including preparation and calibration of the device, correct specimen handling, adherence to identification procedures, and successful data upload to DHIS2. A VCO and a researcher will complete this checklist separately so that we will have 2 observations with which to assess district-level fidelity. Observers will rate protocol adherence as high, medium, or low and will provide narrative field notes describing deviations and potential contributing factors.

Quantitative data collected from VectorCam’s app will be used to assess percent of data completeness, and fidelity will be collected through system-generated usage logs exported monthly for analysis. Completeness of reporting and sustained use metrics will be summarized descriptively. Mixed-effects logistic or ordinal regression models may be used, where appropriate, to explore temporal patterns in completeness of reporting and implementation outcomes related to sustained use while accounting for clustering at the district level.

Throughout the study period, we will use a cost-tracking system to capture direct and indirect costs associated with VectorCam implementation in each district. Cost data will be collected prospectively and will include expenses related to procurement of hardware and consumables, training and supervision activities, technical support, and system maintenance. Financial records, procurement invoices, and project budgets will be reviewed to ensure comprehensive accounting of expenditures. Health economists on the study team will use these data to develop annual and multiyear budget projections, estimate total annual implementation costs, and calculate operational cost savings that result from replacement of manual surveillance methods. These models will generate 1-year, 3-year, and 5-year budget projections to inform national malaria control planning.

Lastly, to ensure transparent reporting of changes to the package over time, we will systematically document all modifications to the intervention and implementation strategies using the FRAME-IS [34]. Throughout implementation, project staff and implementing partners will record proposed or observed changes during routine monitoring and bi-weekly coordination calls. Each adaptation will be documented on a structured form aligned to FRAME-IS domains: (1) the nature of the modification (content, context, personnel, or delivery mode); (2) the level at which the change occurred (individual provider, facility, district, or system level); (3) whether the modification was planned or reactive; (4) the goal of the change, including improving feasibility, acceptability, fidelity, reach, or equity; (5) the decision-making process and actors involved; and (6) the extent to which the change was fidelity-consistent with core program components. We will then categorize adaptations into higher-level themes to enable comparison and identify patterns in how the implementation strategies evolved over time. This process will ensure transparent reporting of adaptations and allow linking of modifications to implementation outcomes and contextual drivers.

### Aim 3: Evaluation of Effectiveness

Effectiveness of the VectorCam intervention (as delivered with implementation strategies) in maintaining accuracy, improving time allocation metrics, and supporting operational use of surveillance data will be assessed with a combination of KIIs, quantitative analyses of system data logs, and qualitative interviews with national and district-level decision-makers. This aim is designed to generate preliminary evidence regarding VectorCam’s performance under ideal implementation conditions and whether the task-shifting model is associated with improvements in data quality and timelier, evidence-based decision-making relative to microscopy-based surveillance. Routine microscope-based entomological surveillance conducted by district entomology teams serves as the comparator condition, as it represents the standard of practice within Uganda’s national malaria surveillance system.

Methods of data collection for Aim 3 include:

Pre- and post-KIIs to evaluate time allocation with usersApp-recorded data logging time spent per mosquito identification eventMolecular analysis comparisonKIIs with national and district-level decision-makers on operational effectiveness and data useNMED quarterly meeting attendance and observational checklist

Pre- and postimplementation interviews with VHTs and VCOs will be used to assess the time required for mosquito identification and data submission. This tool is designed to be utilized at the same time point as the pre- and post-KIIs for data collection within Aims 1 and 2. Participants will be asked to describe the average time spent on identification tasks before and after the introduction of VectorCam, including steps related to specimen preparation, processing, and reporting. Questions on the KII guides differ for VHTs and VCOs in order to capture changes to workflow based on the task-shifting model.

Quantitative data on actual time spent per mosquito identification event will be extracted from VectorCam usage logs over the study period. Logs will include timestamps marking initiation of identification, confirmation of results, and data upload.

For the molecular analysis comparison, accuracy of mosquito species identification using VectorCam will be evaluated by comparing system-generated identifications to a gold-standard reference. Molecular identification will serve as the primary gold standard, using polymerase chain reaction (PCR) when species-specific reagents are available and sequencing when they are not. A random subset of 500 specimens collected during routine surveillance will be selected for molecular validation. This sample size was selected to provide sufficient precision for estimating identification accuracy under routine implementation conditions. Based on the 93% species identification accuracy observed in the previous RCT, a validation sample of 500 specimens yields an approximate 95% CI with a margin of error of +/- 2.2 percentage points around the overall accuracy estimate. These estimates will be used to characterize VectorCam performance descriptively where sample sizes are sufficient, recognizing that precision will vary by the number of specimens available for each species. These specimens will be analyzed independently by an entomologist blinded to the VectorCam results and PCR findings. Accuracy will be defined as the proportion of VectorCam identifications that match PCR results when available, or morphologic identification otherwise. In addition, model performance will be evaluated using standard classification metrics from an AI perspective. In addition to this primary accuracy measure, performance will also be evaluated using standard metrics, including precision, recall, and the *F*_1_-score, which together provide a balanced assessment of how well the model identifies mosquito species.

Next, we will explore VectorCam’s operational effectiveness and data use on malaria control decision-making by interviewing 8-10 MOH-NMED staff and District Health Officers. An interview guide was developed to facilitate the KIIs with national and district-level decision makers to collect qualitative information regarding operational effectiveness and VectorCam data use. The NMED groups that will be interviewed will either have routine interactions with the entomology database, responsibilities for improving the database, and/or responsibilities that involve using the database to make decisions about malaria control programs, including roles such as the Director of the National Malaria Program, Information Technology Senior Developer, lead entomologists, and coordinators of routine surveillance activities. Interviews will explore perceptions of the reliability and utility of VectorCam data, comparisons to previous surveillance approaches, and examples of how data informed vector control interventions or planning. Interviews will be conducted a minimum of 6 months after implementation in each district cohort to allow sufficient time for data review and use.

Lastly, a researcher from either Makerere University or Johns Hopkins University will attend NMED’s quarterly meetings and use the NMED quarterly meeting attendance and observational checklist to document how the VectorCam data are reviewed and used during routine decision-making processes. The checklist will capture whether VectorCam data were presented, discussed, or referenced in relation to surveillance planning, vector control activities, resource prioritization, or other operational decisions. Findings from these observations will be triangulated with key informant interviews to assess the perceived utility and operational use of VectorCam data.

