Aim 3: technical effectiveness	Validation subset with VectorCam, routine method, and PCR^i^ (or equivalent)	Sensitivity, specificity, PPV^j^, NPV^k^, F1-score, agreement	Diagnostic accuracy analysis with 95% CIs; paired comparison when both methods are available; descriptive comparison of classification performance
Aim 3: operational effectiveness and data use	Quarterly NMED^l^ meeting attendance checklist KIIs to measure time allocation with users KIIs with district and national decision-makers	Use of data in planning; reporting timeliness Time allocation; task-shifting model metrics Data usage by decision-makers; impact on malaria control actions	Descriptive comparisons of time allocation metrics and data-use indicators across districts and rollout phases; mixed effects regression for time metrics; qualitative thematic analysis of data-use pathways

^a^CFIR: Consolidated Framework for Implementation Research.

^b^ERIC: Expert Recommendations for Implementing Change.

^c^KII: key informant interview.

^d^Pre and postinterviews are conducted 1-week after training and 3 months after implementation.

^e^IDI: in-depth interview.

^f^VCO: vector control officer.

^g^VHT: village health team.

^h^FRAME-IS: Framework for Reporting Adaptations and Modifications–Enhanced for Implementation Strategies.

^i^PCR: polymerase chain reaction.

^j^PPV: positive predictive value.

^k^NPV: negative predictive value.

^l^NMED: National Malaria Elimination Division.

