Quantitative data will be derived from structured surveys, field observation checklists, costing databases, and the data dashboard, which tracks key metrics such as data completeness. Descriptive analyses will be conducted to summarize key variables, including measures of data completeness, usage frequency, and accuracy. Implementation outcomes will be assessed using multiple complementary indicators and, where appropriate, proportions will be calculated with 95% CIs. Fidelity will be evaluated through both system-generated metrics, such as completeness of required data fields, and observational assessments of protocol adherence. Patterns of system use will be examined longitudinally to assess trends over time and variation across districts. Descriptive summaries will be generated by district and rollout wave, including district-quarter trend plots to visualize changes over time.

Cost analysis will be conducted from the program perspective, with scenario analyses for broader health system scale-up. An ingredients-based costing approach will be used to estimate startup and recurrent costs, including hardware, consumables, training, supervision, maintenance, connectivity, and technical support. Capital items will be annualized over their useful life using a standard discount rate. Unit costs will be reported per district covered, per user trained, and per identification event completed. Budget impact models will be developed to project costs under different scale-up scenarios, incorporating both observed expenditures and anticipated changes in resource requirements. Sensitivity analyses will test uncertainty in key assumptions.

Effectiveness outcomes will be assessed using both quantitative and qualitative data. Time allocation will be evaluated through both self-reported data (collected via the pre- and post- KIIs) and system-recorded measures of time spent on surveillance activities. To evaluate the task-shifting model that VectorCam used, time allocation comparisons will be made across pre- and postimplementation periods. Accuracy of mosquito identification will be assessed by comparing VectorCam outputs to the gold-standard molecular identification (PCR or sequencing for species for which PCR reagents are not available). Qualitative data from interviews with decision-makers will be analyzed thematically to assess the perceived utility of surveillance data for decision-making using the same codebook as other qualitative data collection tools.

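### The accuracy definition falls back to morphologic identification where the plan elsewhere requires sequencing, so the reference standard for the main accuracy measure is contradictory

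*Protocol article*

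**What the plan says.** The reference standard is described in three places in the protocol article.

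- **Aim 3: Evaluation of Effectiveness, first statement.** Molecular identification is the primary gold standard, "using polymerase chain reaction (PCR) when species-specific reagents are available and sequencing when they are not".
- **Aim 3, operative definition, later in the same paragraph.** "Accuracy will be defined as the proportion of VectorCam identifications that match PCR results when available, or morphologic identification otherwise". Sequencing is not mentioned. The article treats this as its main accuracy measure and adds precision, recall and F1 to it.
- **Data Management and Analysis.** VectorCam outputs are compared with "gold-standard molecular identification (PCR or sequencing for species for which PCR reagents are not available"). There is no morphologic fallback.

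Three other statements bear on the consequences.

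- Aim 3 names the comparator: "Routine microscope-based entomological surveillance conducted by district entomology teams serves as the comparator condition".
- Table 1 (Study Design Overview) describes a validation subset with VectorCam, the routine method and PCR or an equivalent, and plans a "paired comparison when both methods are available".
- Aim 3 says of the validation specimens: "These specimens will be analyzed independently by an entomologist blinded to the VectorCam results and PCR findings". It does not say whether this reading, or the routine district reading, is the morphologic fallback.

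**The concern.** An analyst holding a specimen of a species without PCR reagents finds two instructions. One leads to a sequence, the other to a microscope reading. The same 500 specimens can then yield different values of accuracy, sensitivity, specificity, PPV, NPV and F1, depending on which sentence is followed.

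Under the fallback the headline figure also becomes a mixture. For some specimens it measures whether VectorCam is right. For the others it measures whether VectorCam agrees with a morphologic reader who can be wrong. The two parts cannot be separated once they are pooled.

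Morphology is, in addition, the method that VectorCam is to be compared with. If the fallback reading were the routine one, the paired comparison in Table 1 would lose its neutrality on those specimens.

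**Working it through.** **1. The plan's own figure.** Inputs from Aim 3: n = 500, accuracy 93%, 95% confidence. Half-width = 1.96 × √(0.93 × 0.07 / 500) = 0.0224, or 2.24 points. The stated ±2.2 points reproduces. The 93% was measured in the earlier randomized trial against entomological identification (Introduction, section on the field tool), so it is not itself on the molecular scale.

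**2. VectorCam accuracy under the fallback.** Let a be VectorCam's true accuracy, taken as 0.93 in all specimens, f the share scored against morphology, m the accuracy of morphology, and g the agreement of VectorCam with morphology.

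Apparent accuracy = (1 − f) × a + f × g, where g lies between a + m − 1 (the two never err on the same specimen) and 1 − |a − m| (errors shared as far as possible).

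The article gives neither f nor m. The values below are assumptions.

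| f | m | g, range | Apparent accuracy |
|---|---|---|---|
| 10% | 95% | 0.88 to 0.98 | 92.5% to 93.5% |
| 20% | 90% | 0.83 to 0.97 | 91.0% to 93.8% |
| 30% | 90% | 0.83 to 0.97 | 90.0% to 94.2% |
| 50% | 85% | 0.78 to 0.92 | 85.5% to 92.5% |

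Example, third row: 0.7 × 0.93 + 0.3 × 0.83 = 0.900, and 0.7 × 0.93 + 0.3 × 0.97 = 0.942. Shared errors push the figure up and separate errors push it down. The shift is zero if f = 0 or m = 1.

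**3. The paired comparison, if the routine reading were the fallback.** On fallback specimens microscopy would score 100% and VectorCam would score g. The shift in the difference (VectorCam minus microscopy) is

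−f × [(1 − g) + (VectorCam true accuracy − microscopy true accuracy)],

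with both true accuracies taken on the fallback specimens. Splitting disagreements by who is right, the bracket equals 2 × P(VectorCam right, microscopy wrong) + P(both wrong, differently). It is never negative, so the shift can only favour microscopy.

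Take g = 0.93 and f = 30%, both assumed:

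- Microscopy perfect: bracket = 0.07 − 0.07 = 0, shift 0.
- VectorCam 93%, microscopy 95%: −0.3 × (0.07 − 0.02) = −1.5 points.
- Equal true accuracy: −0.3 × 0.07 = −2.1 points.
- VectorCam perfect: −0.3 × (0.07 + 0.07) = −4.2 points.

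Microscopy's own apparent accuracy would be (1 − f) × m + f. At f = 20% and m = 90% it would read 92.0% instead of 90.0%.

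**4. Precision if only molecularly resolved specimens are scored.** The formula of step 1 gives 2.24 points at n = 500, 2.36 at 450, 2.50 at 400, 2.67 at 350 and 3.16 at 250.

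**The case against.** The best defence is that PCR is used as shorthand for any molecular result. Table 1 allows PCR or an equivalent, the blinding sentence speaks only of PCR findings although sequencing is planned, and calling molecular identification the primary gold standard leaves room for a secondary one. On that reading morphology serves only when no molecular result exists, and the fallback share may be small. This is plausible, but it does not remove the conflict. The analysis section contains no morphologic fallback at all, and a literal reader would skip sequencing.

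Three stronger conclusions are tempting, and the documents do not support them.

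- *The comparator becomes its own reference.* The definition scores only VectorCam. Exact self-reference needs the routine district reading to be the fallback, and Aim 3 mentions an independent entomologist, blinded to VectorCam and PCR, whose reading may be the one meant. Table 1 also does not say which reference the paired comparison uses on fallback specimens.
- *The bias in the paired difference is 7 points times the fallback share.* That holds only if agreement is 93% and both methods are equally accurate on those specimens. Step 3 shows how far other assumptions move it. The ±2.2-point margin is also for a single proportion, so it is no yardstick for a paired difference.
- *Fallback specimens are the harder cases.* Nothing in the article says so. Lack of a PCR reagent is not the same as difficulty of identification.

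It also stands that technical accuracy belongs to the secondary aim, that no formal hypothesis test is planned, and that Challenges and Limitations calls the effectiveness results preliminary and descriptive. This lowers the severity. It does not excuse two rules for one measure.

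**Conclusion.** The point holds as a contradiction in the reference standard. The operative definition of accuracy omits sequencing and admits morphology, while two other statements make the reference molecular throughout. This is not detail left to an analysis plan, because the article itself states the scoring rule in incompatible ways.

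A reader might infer that VectorCam accuracy will be biased. The documents support only a risk of bias, of unknown direction and size. With a true accuracy of 93% and the assumed fallback shares and morphologic error rates above, the shift runs from at most half a point either way to several points downward, which can exceed the stated margin. For the paired comparison the direction is fixed, towards microscopy, but only if the routine reading is the fallback, and the article leaves that open. Severity is moderate.

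**What to change.** 1. **Reword the definition in Aim 3**, for example: *Accuracy is the share of VectorCam calls that agree with the molecular identification, meaning PCR, or sequencing for species without a PCR reagent.* This brings it into line with the first statement in Aim 3 and with Data Management and Analysis.
2. **Report specimens with no molecular result separately**: their number and predicted class, their agreement with morphology, and best-case and worst-case bounds on overall accuracy that count all of them as matches or as mismatches.
3. **State that the routine microscopy reading never serves as the reference in the paired comparison** of Table 1.

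Sequencing is already planned, so this is a change of wording and of the scoring rule, not a new procedure. One cost is precision: 2.50 points with 400 resolved specimens, against 2.24 with 500. The other is possible selection if unresolved specimens differ from the rest. The bounds would show this but not correct it, and they are informative only when few specimens are unresolved. With 93% accuracy among the resolved, 4% unresolved gives 0.96 × 93 = 89.3% to 89.3 + 4 = 93.3%. With 20% unresolved, the bounds are 0.80 × 93 = 74.4% to 74.4 + 20 = 94.4%.
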